### 3.11 Statistical analysis

**
*3.11.1 Proposed analyses*
**

**3.11.1.1
Part A analyses
**

We will compute the area under the curve for the melatonin profile using the trapezoidal method and also compute the percentage difference between the healthy control group and the BD lithium therapy group, as well as between the healthy control group and the BD non-lithium treatment group. We will then use one-way ANOVA (or Kruskal-Wallis) with post-hoc analyses (Tukey) across the three groups, as well as undertaking general linear model analyses controlling for potential confounding variables such as age, sex, ethnicity, educational attainment, employment status, socioeconomic status, smoking status, alcohol use, sleep quality, chronotype, psychiatric history, medication use and score on the Alda lithium response scale. 

**3.11.1.2
Part B analyses
**

Statistical analyses for the various measures (pupillary response, colour perception, spatiochromatic processing, visual evoked potentials) across the three groups will be performed using linear mixed effect models with healthy control group set as the baseline (i.e., zero) level for all the comparisons. Models will also be evaluated for the contribution of confounding factors, including age, sex, ethnicity, educational attainment, employment status, socioeconomic status, smoking status, alcohol use, sleep quality, chronotype, psychiatric history and medication use and score on the Alda lithium response scale.

**3.11.1.3
Part C analyses
**

We will test the hypothesis that people with BD have significant differences in structural and functional measures of the retina and in the trajectory of change compared to controls. Additionally, we will assess whether individuals with BD who are taking lithium have an attenuated trajectory of change compared to those with BD on other medications. Student’s t-test and generalised estimation equations will be used to examine differences in retinal measures and psychophysical thresholds between the three participant groups. Spearman’s rank correlation coefficient will be used to investigate associations of retinal measures and psychophysical thresholds with other key parameters from the study data, including confounding demographic and clinical factors. Trajectory analysis will be used to assess changes in retinal parameters and psychophysical thresholds over time and how effective this approach is at stratifying participants.

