### 3.6 Study population

**
*3.6.1 Sample size calculation*
**

This study will assess 180 participants:

*n*=60 with bipolar disorder and currently on lithium therapy
*n*=60 with bipolar disorder and not taking lithium
*n*=60 healthy controls with no history of mental illness and no first-degree family history of mental illness

The required sample size for this study is calculated from melatonin measures relevant to Part A. This sample size is sufficient for both Part B and Part C of the project (see below). Sex and gender differences were not taken into consideration in study design or sample size calculations because there is no conclusive evidence of sex or gender differences in the primary study outcome measures.

**3.6.1.1
Part A Sample Size Calculation
**

Our subjects of interest are BD patients versus controls, with the BD group sub-divided into two groups: one where BD subjects are on lithium therapy and another where BD subjects are not taking lithium. Based on previous reports of light-induced melatonin suppression in BD (
Hallam *et al.*, 2009) we expect a difference of approximately 40–50% (Cohen’s d effect size 0.5–0.6) between the BD lithium group and the BD non-lithium group. As such, for 80% power with an alpha of 5%, we will need 42 participants in each of the three groups. Allowing for incomplete data collection in up 30% of participants, this means that we will recruit 60 participants in each group.

**3.6.1.2
Part B Sample Size Calculation
**

With this sample size (N=180 participants across three groups), a two-sided between-subjects t-test at 80% power with an alpha level of 0.05 will be able to reliably detect an effect size of d=>0.52, equivalent to a difference of 0.52 of a standard deviation (i.e., medium effect size). Comparably, a between-subject ANOVA with three groups would be able to detect an effect size of f=>0.23. For a clinical study of this kind, this represents a very high level of sensitivity. As a minimum, it will allow us to provide a more definitive characterisation of the observed phenomena than previous studies in this field. As a comparison, studies with groups of 20 participants, which are common in the existing literature, are capable of detecting an effect of d=>0.9 (two groups) or f=>0.41 (three groups), which are large effect sizes.

**3.6.1.3
Part C Sample Size Calculation
**

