### 3.10 Outcome measures

**
*3.10.1 Primary outcome measures*
**

**3.10.1.1
Part A
**

Difference in absolute change in plasma melatonin levels in response to light stimulation protocol between the 3 study groups.

**3.10.1.2
Part B
**

Difference in pupillometry, visual evoked potential, and chromatic discrimination/detection measures between the 3 study groups.

**3.10.1.3
Part C
**

Retinal structure differences between the 3 groups assessed over time

**
*3.10.2 Secondary outcome measures*
**

**3.10.2.1
Part A
**

To determine absolute differences in the following measures between the 3 study groups:

ALDA scale (Bipolar Disorder groups only)PSQI total score for sleep qualityMCTQ total score for chronotypeMEQ total score for chronotypeWHODAS 2.0 total score for global functionm-SPAQ total score for seasonal sensitivity

**3.10.2.2
Part B
**

Correlation of primary outcome measures with other, non-retinal measures acquired in the study (e.g. questionnaires, medical history), as well as with each other.

**3.10.2.3
Part C
**

Secondary outcomes include cross-sectional and longitudinal differences in retinal vascular metrics; retinal layer thickness; small vessel metrics; eye biometrics; visual field metrics. These outcomes will be correlated with other, non-retinal measures acquired in the study.

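### Part A names Tukey as the only follow-up to Kruskal-Wallis as well as to ANOVA, so on the rank branch the pairwise step tests a different hypothesis from the overall test (minor)

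*Protocol article*

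**What the plan says.** Section 3.11.1.1 first fixes the analysed quantity: "We will compute the area under the curve for the melatonin profile using the trapezoidal method". Percentage differences follow, but only for each bipolar group against controls. The group comparison is then: "We will then use one-way ANOVA (or Kruskal-Wallis) with post-hoc analyses (Tukey) across the three groups". Tukey is the only follow-up named, and the sentence applies it to both overall tests. Covariate-adjusted general linear models are added, with no transformation stated.

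The second Part A objective (3.1.1) compares bipolar participants on lithium with those not on it. The sample size in 3.6.1.1 rests on that same pair: "we expect a difference of approximately 40–50% (Cohen’s d effect size 0.5–0.6) between the BD lithium group and the BD non-lithium group". The primary outcome in 3.10.1.1 is "Difference in absolute change in plasma melatonin levels in response to light stimulation protocol between the 3 study groups".

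**The concern.** Tukey's procedure tests equality of raw means against a common within-group variance. Kruskal-Wallis tests whether the groups' rank distributions differ. The usual reason to move from ANOVA to Kruskal-Wallis is doubt about the raw scale or the shape of the data. The article gives no reason, so this is an inference. If that is the reason, following Kruskal-Wallis with Tukey brings the doubtful scale back at the next step.

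In a three-group design this affects the main question. The overall test cannot say whether lithium and non-lithium participants differ. The percentage differences named in 3.11.1.1 do not cover that pair either. Among the unadjusted analyses, only the post-hoc step answers Objective 2. At stake is a Part A result in which the overall test is significant, no pair is, and the reason is that the two steps used different scales.

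**Working it through.** **The plan's own figure.** 3.6.1.1 states "for 80% power with an alpha of 5%, we will need 42 participants in each of the three groups". A three-group ANOVA with two equal groups and the third 0.6 SD away has f = 0.6 × √2 / 3 = 0.283. At 80% power and alpha 5% this needs 41.2, so 42 per group, which matches. Also 42 / 0.70 = 60. (At d = 0.5 the same calculation gives 59, so 42 goes with the upper end of the stated range.) I take 42 per group as the evaluable number.

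**Inputs that must be assumed.** The article gives no mean, SD or distribution for the melatonin AUC. To get a working spread I read the 40–50% as a relative difference in means of a positive quantity: SD / reference mean = 0.40 / 0.5 = 0.80, or 0.50 / 0.6 = 0.83. I used a 40% difference (bipolar group means 0.6 and 1.0) and a coefficient of variation of 0.80.

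**Simulation.** 20,000 trials per row, 42 per group, alpha 5%. The control mean was placed at the lower bipolar mean, midway, or at the upper mean. The normal rows use SD 0.80 in every group (d = 0.5). Entries are percentages of all trials.

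| Data | Control mean | Kruskal-Wallis significant, no Tukey pair | Kruskal-Wallis significant, no Dunn-Holm pair | Lithium v non-lithium power, raw Tukey | Same, Dunn-Holm |
|---|---|---|---|---|---|
| Lognormal | lower | 7.2 | 1.7 | 77 | 81 |
| Lognormal | midway | 12.3 | 1.9 | 70 | 80 |
| Lognormal | upper | 10.7 | 1.6 | 63 | 82 |
| Gamma | lower | 1.6 | 3.2 | 75 | 60 |
| Gamma | midway | 3.5 | 3.0 | 68 | 59 |
| Gamma | upper | 3.6 | 3.2 | 61 | 61 |
| Normal | lower | 2.9 | 3.5 | 46 | 44 |
| Normal | midway | 3.2 | 3.4 | 47 | 43 |

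Independent runs put the lognormal range in the third column at about 8–12%, so it is stable to about a percentage point.

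**Reading the table.** The mismatch produces the significant-overall, no-pair result mainly when the tail is heavy (lognormal). There a rank-based follow-up cuts it to about 2% and also raises power for the key pair. Under gamma data with the same means and spread, the two follow-ups differ little on this measure, and raw Tukey has equal or higher power for the key pair, by up to 15 points (75% v 60%).

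**The ANOVA branch.** ANOVA was significant with no Tukey pair in only about 1.5–2% of the same trials. The defect belongs to the Kruskal-Wallis branch.

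**False positives.** With no group difference, raw ANOVA rejected in 4.1–5.0% of trials and Kruskal-Wallis in 4.7–5.1%. Neither test alone inflates the type I error.

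**The case against.** The strongest reply is that this is one phrase under a list of proposed analyses in a condensed article. The rule for choosing between the tests, and a rank-based follow-up, are ordinary content for an analysis plan that is not shown. Tukey may also have been meant for ANOVA only, or as shorthand for a Tukey-type comparison of ranks. The adjusted linear models give a second route to the lithium contrast. Much of this stands. The missing selection rule is not a finding, and the document does not say that the test will be picked after seeing the data. What remains is what the sentence states: one follow-up, attached to both tests, and suited to only one of them.

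A reader might go further and infer that the plan's own figures show a strongly right-skewed AUC, so that the rank branch is bound to be reached and a log-scale analysis would recover lost power. The documents do not support that, for three reasons.

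- The 40–50% is tied to suppression ("Based on previous reports of light-induced melatonin suppression in BD"), not to the AUC, and may be in percentage points. In that case no coefficient of variation follows.
- The power gain depends on the distribution assumed. For lithium versus non-lithium, log-scale Tukey reached 82–83% against 62–78% for raw Tukey under lognormal data, but 54–55% against 61–75% under gamma data with the same means and spread.
- The primary outcome in 3.10.1.1 is a signed absolute change. It can be zero or negative and cannot be logged directly.

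**Conclusion.** The point holds and is minor. As written, 3.11.1.1 pairs a rank-based overall test with a raw-mean pairwise test, and the pairwise test carries Objective 2. If the Kruskal-Wallis option is used and the data are about lognormal with a coefficient of variation near 0.80, roughly one trial in eight to one in fourteen (7–12%) would show a significant overall test with no significant pair. A matched follow-up brings that to about 2%. If the data are closer to gamma or normal, the choice of follow-up makes little difference to this measure (about 2–4% either way), and the case for the change is coherence of hypotheses rather than performance. The sizes rest on an assumed relative difference, spread and distribution. The mismatch itself rests only on the wording.

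**What to change.** In 3.11.1.1, tie Tukey to the ANOVA or linear-model branch only. State that if Kruskal-Wallis is used, it is followed by a rank-based pairwise procedure, either Dunn's test with a multiplicity adjustment or Steel-Dwass.

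This changes wording only. It needs no new data, participants or visits, and the article reports the study as still recruiting. The downside is that, on the rank branch, pairwise power can fall somewhat below raw Tukey if the data are only moderately skewed, as the gamma rows show.

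A log-scale model with back-transformed percentage differences is an option to justify, not a required correction. It needs a positive quantity to analyse, and it would replace the absolute change of 3.10.1.1 with a ratio, which changes the estimand.

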### 3.12 Dissemination plan

The results of the HELIOS-BD study will be written up for publication in relevant scientific journals. Participants will receive a results summary letter once the study results are available, detailing the findings of the study and once again thanking them for their participation. Results from the study will additionally be summarised on the study website (
www.heliosbd.com).

### 3.13 Adverse events

Participants will be encouraged to contact the research team at any time should they experience any problems during or following their participation. All adverse events and adverse reactions will be recorded using the appropriate ‘
*Adverse Event or adverse reaction Log*’. Adverse events may occur in relation to procedures of Part A and Part B: telemetric pill ingestion; blood sampling/draws; light stimulation; and/or bilateral ocular application of pupil dilator medication. Serious adverse events (SAE’s) reporting will follow HRA procedure for REC notification and subsequent action, and will include any Serious Adverse Events (SARs) or Suspected SUSARs, as defined below.

**
*3.13.1 Definitions*
**

An adverse event (AE) is an untoward medical occurrence in a study participant.

An adverse reaction (AR) is any untoward and unintended response which is related to the outcome data collection for that participant. A serious adverse reaction (SAR) is any AR that:

results in death of the clinical trial participant; is life threatening*;requires in-patient hospitalisation or prolongation of existing hospitalisation^;results in persistent or significant disability or incapacity;consists of a congenital anomaly or birth defect;results in any other significant medical event not meeting the criteria above.

A suspected unexpected serious adverse reaction (SUSAR) is any AR that is classified as serious and is suspected to be caused by the outcome data collection.

*Life-threatening in the definition of an SAE or SAR refers to an event where the participant was at risk of death at the time of the event. It does not refer to an event which hypothetically might have caused death if it were more severe.

^Any hospitalisation that was planned prior to randomisation will not meet seriousness criteria. Any hospitalisation that is planned post randomisation will meet the seriousness criteria unless it does not constitute an untoward medical occurrence (e.g. cosmetic elective surgery, social and/or convenience admission, etc.).

### 3.14 Good clinical practice

**
*3.14.1 Ethical conduct*
**

The study will be conducted in accordance with the principles of the International Conference on Harmonisation Tripartite Guideline for Good Clinical Practice (ICH GCP). Before the study can commence, all necessary approvals will be obtained and any conditions of approvals will be met.

**
*3.14.2 Informed consent*
**

The Investigator is responsible for ensuring informed consent is obtained before any study specific procedures are carried out. The decision of a participant to participate in clinical research is voluntary and should be based on a clear understanding of what is involved. Participants must receive adequate oral and written information – appropriate Participant Information and Informed Consent Forms will be provided. The oral explanation to the participant will be performed by the Investigator or qualified delegated person, and must cover all the elements specified in the Participant Information Sheet and Consent Form. The participant must be given every opportunity to clarify any points they do not understand and, if necessary, ask for more information. The participant must be given sufficient time to consider the information provided. It will be emphasised that the participant may withdraw their consent to participate at any time without loss of benefits to which they otherwise would be entitled. The participant will be informed and agree to their medical records being inspected by regulatory authorities and representatives of the Sponsor(s). The Investigator or delegated member of the study team and the participant will sign and date the Informed Consent Form(s) to confirm that consent has been obtained. The original will be signed in the Investigator Site File (ISF). The participant will receive a copy of the signed consent form and a copy will be filed in the participant’s medical notes and sent to their GP.

**
*3.14.3 Confidentiality*
**

All laboratory specimens, evaluation forms, reports, and other records must be identified in a manner designed to maintain participant confidentiality. All records must be kept in a secure storage area with limited access. Clinical information will not be released without the written permission of the participant. The Investigator and study site staff involved with this study may not disclose or use for any purpose other than performance of the study, any data, record, or other unpublished information, which is confidential or identifiable, and has been disclosed to those individuals for the purpose of the study. Prior written agreement from the Sponsor or its designee must be obtained for the disclosure of any said confidential information to other parties.

**
*3.14.4 Data protection*
**

All Investigators and study site staff involved with this study must comply with the requirements of the appropriate data protection legislation (including the General Data Protection Regulation and Data Protection Act) with regard to the collection, storage, processing and disclosure of personal information. Computers used to collate the data will have limited access measures via user names and passwords. Published results will not contain any personal data that could allow identification of individual participants.

**
*3.14.5 Study record retention*
**

Personal data will be stored for 15 years after study completion on the University of Edinburgh DataVault. For one year following study completion, data will be held in pseudonymised format. After deletion of identifiable data (one year after study completion), the study dataset will effectively become anonymised. Anonymised digital data will be kept for a period of 14 years after the deletion of identifiable data. When the minimum retention period has elapsed, study documentation will be destroyed with permission from the Sponsor.

**
*3.14.6 End of study*
**

The end of study is defined as the last participant’s last visit. The Investigators and/or the Sponsor(s) have the right at any time to terminate the study for clinical or administrative reasons. The end of the study will be reported to the REC, and R&D Office(s) and Sponsor(s) within 90 days, or 15 days if the study is terminated prematurely. The Investigators will inform participants of the premature study closure and ensure that the appropriate follow up is arranged for all participants involved. End of study notification will be reported to the Sponsor(s) via email to
[contact]. A summary report of the study will be provided to the REC within 1 year of the end of the study.

### 3.15 Ethical approvals

The HELIOS-BD study received a favourable ethical opinion from the South East Scotland Research Ethics Committee on 20/10/2023 (23/SS/0104). NHS Lothian R&D approvals were granted on 09/11/2023. The HELIOS-BD study is co-sponsored by the University of Edinburgh and NHS Lothian.

### 3.16 Ethical considerations of the research

1. Ensuring inclusive and representative recruitment:

Our recruitment methods are based on voluntary contact from interested individuals who have been informed of the study either through established research and mental health organisations, or via social media. However, it is known that particular identities are under-represented in medical research, with serious consequences for equitable healthcare. In particular, people from minoritised ethnic groups, people at socioeconomic disadvantage and people with minoritised sexualities and gender identities are under-represented and under-served by research. The reasons for this are many and varied. In this study, we aim to achieve a representative and diverse study population, with equal representation of men and women. We will advertise the study widely, and we will recruit thoughtfully to ensure our sample is representative of the bipolar disorder population in Scotland. We will also provide reimbursement for caring costs (e.g. childcare) to remove barriers to participation for those with caring responsibilities.

2. Preventing undue incentivisation due to participation payments:

Study participants will be reimbursed for their time and travel expenses. However, it is important that financial benefits do not inappropriately incentivise individuals to participate in the research when it is not in their best interests. The participation payment will therefore be advertised in a neutral tone in any study advert materials and in the Participant Information Form. We recognise that offering payment for study participation may increase the possibility of dishonesty from people who want to participate in the research, in order to increase their chances of enrolment. We will address this by using NHS-linked recruitment methods and by corroborating information with medical notes where necessary.

3. Risks and adverse events associated with study procedures:

Some of the study procedures carry risks for adverse events; for example, participants may experience short-term discomfort during the study procedures required for this study. Associated risks will be minimised by ensuring that experienced staff are appropriately trained to conduct the procedures, and that participants are fully informed of all procedures. Participants will be instructed to inform the research team of any health issues or concerns which arise during the study, to make sure they are appropriately cared for. A wellbeing follow-up call is scheduled for all participants 3 days following their final overnight stay to make sure there are no negative impacts of the light delivery protocol.

Further to this, there is a small risk that incidental findings may be identified on the retinal images which may require further investigation. We anticipate the rate of significant or urgent findings to be <1%. Each participant will be told of this risk, as well as it being stated on the participant information sheet. Should we observe unusual signs in the images that might signs of eye problems, anonymised images will be reviewed by the ophthalmologist on our team for checking of incidental findings. If we were to observe any such findings then an appropriate member of the study team would discuss this with the participant and inform their GP so that appropriate further tests and treatments could be arranged as necessary.

4. Making sure the research is relevant and acceptable to people with bipolar disorder:

It is important that the research we conduct is relevant and acceptable to people with bipolar disorder. We are in ongoing consultation with the HELIOS-BD Lived Experience Advisory Panel (LEAP) and volunteers from Bipolar Scotland to make sure this is the case. The study design has already benefited from input from people with lived experience of bipolar disorder.

